### User involvement

User involvement is central to the INACT study. The research team has already worked with North Thames Applied Research Collaborative Patient and Public Involvement and Engagement (PPIE) group, as well as the Social Prescribing Youth Network’s Youth Advisory Group (YAG) to develop this protocol. Both groups were positive about SP and advocated for a ‘school-based’ approach over other options presented. There was interest from members of both groups in providing input into the INACT study, including reviewing study documents, interpretation of findings, co-authoring papers, as well as dissemination of results in creative and accessible formats (e.g., vlogs for YP). PPIE stakeholders will meet monthly at the start of the project to facilitate start up before moving to quarterly meetings.

### Ethical considerations

Ethical approval for this study has been obtained from the UCL Research Ethics Committee (6735/017). A copy of the ethics application is in the S3 File. As per similar studies [30,31], and in line with the UK Department for Educations’ procedures [52], opt out consent will be sought from parents/guardians, recognising their responsibilities to their YP, whilst maintaining YP autonomy through their assent. UCL Research Ethics Committee approved the full consent procedure, including the use of opt-out parental consent. Information Sheets in age-appropriate language will be co-developed in collaboration with the YAG. Participants will have the right to withdraw at any point, without needing to give a reason. Encrypted Dictaphones or secure videocall platforms will be used for all interviews. Questionnaire data will be anonymised and qualitative data will be pseudonymised. Personal data will be stored securely on the UCL Data Safe Haven conforming to NHS Digital’s Information Governance Toolkit.

### Monitoring adverse events

The ongoing conduct and progress of this study will be monitored by an independently chaired Data Monitoring Committee (DMC) and Trial Steering Group. The DMC will include a statistician, clinician and lay member of the public all of whom have no conflict of interest with INACT. The DMC is independent of the Sponsor and the charter is available on request from the corresponding author. The Steering Group will consist of academics, service users, clinicians and those involved in policymaking.

Monitoring of Adverse Events (AE), defined as a negative, emotional and behavioural occurrence, or sustained deterioration in a research participant, will be captured during INACT. This includes Serious Adverse Events (SAE) which are a threat to life: suicidal ideation, suicidal intent, hospitalisation due to psychiatric use of substances and death including suicide. Other AEs, such as violent behaviour, self-harm, physical injury, or any other event that an individual feels is important to report, will also be captured.

LWs and School Safeguarding Leads will judge whether they believe the AE is likely related to the intervention. On becoming aware of SAEs, the Principal Investigator/Deputy Trial Manager will report SAEs or AEs which are likely to be related to the intervention to University College London who is sponsoring the research, the DMC and Steering Committee. Other AEs will be collated and reported quarterly to these groups. School and research safeguarding protocols will also be followed as standard in addition to the reporting and documenting of AEs. Participants will have the right to stop participating in the intervention, and will be made aware of this by LWs and researchers when any AEs are reported. The study sponsor has insurance arrangements in place should participants be harmed as a result of the INACT trial.

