### Intervention and control

SP is a person-centred approach to wellbeing involving the co-development of a non-clinical prescription, between an individual (in this case, YP) and LW, based on the perceived reasons for the referral and the YP’s values, needs and preferences [24]^.^ LWs have an excellent knowledge of their local areas, via community asset mapping and networking, allowing them to connect individuals with different types of support and activities.

The SP intervention used in this study will be ‘YES’: Youth Engagement in Social prescribing. YES has been developed to connect children and young people with forms of support in their communities to improve wellbeing. It has been used nationally, for example as part of the Wellbeing While Waiting programme which is implementing SP for YP on waiting lists for mental health treatment [35].

The SP intervention will range from 6-12 sessions over an 8-week period. Sessions may take place online, via phone call, or in person. As part of the SP process, LWs will draw on psychological skills such as motivational interviewing and behavioural activation [18] as well as employ problem solving and goal setting [36]. Following the identification of individual needs and preferences, the LW will discuss available local activities and informal sources of support with YP that best match their interests and could help them to feel more connected. Then, with the YP’s agreement, the LW will facilitate their engagement with these activities, which could be done via the LW making links with the organisation and/or accompanying the YP to the first session. All LWs will have undergone training [37] and receive supervision from an experienced mental health professional and/or senior LW.

YP in the control group will receive signposting to social and community activities in their local area. This will consist of school pastoral staff providing YP with a leaflet detailing information on the same local sources of support identified by the LW from asset mapping.

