Ability to collect 3-month data from pupils who completed baseline measures	Proportion of young people completing 3 month follow up	55-100%	40-54%	0-39%
Negative consequences of the intervention	Reported negative/adverse effects of social prescribing from young people, school staff or link workers	No evidence of substantially negative effects on young people	–	Evidence of substantially negative effects on young people

***(Rqiii)*** To assess whether power calculation assumptions are realistic, descriptive statistics, and point estimates of the within-person intraclass correlation coefficients (ICCs) for all instruments based on the pilot data will be calculated, as well as a bootstrap study exploring the upper bounds for the ICCs.

Where questionnaire data is missing from participants at random, multiple imputation will be employed. There will be no interim analysis given the short timescale (6 months) that participants are involved in the intervention.

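### The serious adverse event list does not follow its own threat-to-life criterion: self-harm and physical injury are classed as other AEs with no severity qualifier

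*Protocol article*

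**What the plan says.** All of the safety text is in the protocol article under Monitoring adverse events.

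- **Serious events.** SAEs are AEs "which are a threat to life: suicidal ideation, suicidal intent, hospitalisation due to psychiatric use of substances and death including suicide".
- **Other events.** The sentence that follows says: "Other AEs, such as violent behaviour, self-harm, physical injury, or any other event that an individual feels is important to report, will also be captured".
- **Relatedness.** "LWs and School Safeguarding Leads will judge whether they believe the AE is likely related to the intervention".
- **Reporting outside the quarterly cycle.** On becoming aware of events, the Principal Investigator or Deputy Trial Manager "will report SAEs or AEs which are likely to be related to the intervention to University College London", and also to the DMC and Steering Committee.
- **Quarterly route.** "Other AEs will be collated and reported quarterly to these groups".
- **Parallel safeguard.** School and research safeguarding procedures apply as standard, alongside AE reporting.

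For timing, Intervention and control states: "The SP intervention will range from 6-12 sessions over an 8-week period". Procedure gives 3 January 2025 as the intended start of the interventions and 12 November 2024 as the start of baseline data collection.

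**The concern.** The section uses two ways of deciding what is serious, and they do not give the same answer. One is a criterion, threat to life. The other is a list of event types. Suicidal ideation is on the serious list whatever its degree. Self-harm and physical injury are named among the other AEs, with nothing to separate a minor event from a life-threatening one. The only hospitalisation on the serious list is tied to psychiatric use of substances. That phrase is unclear in itself, and it leaves an admission after self-harm or injury without an obvious place.

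The label matters because it decides the reporting route. An SAE goes to the sponsor and the oversight committees when it becomes known. An other AE does so only if it is judged likely related; otherwise it waits for the quarterly collation. The judgement is made by Link Workers, who deliver the intervention, and School Safeguarding Leads, in a trial that Procedure says cannot be blinded. Staff across 12 schools could also file the same event differently, depending on whether they apply the criterion or the list.

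**Working it through.** The plan gives no figure on this point to reproduce. The check sets the text side by side and then does date arithmetic.

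**1. Criterion against lists**

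| Event | By the threat-to-life criterion | By the lists as written |
|---|---|---|
| Suicidal ideation | Depends on the case | SAE |
| Life-threatening self-harm | SAE | Other AE |
| Life-threatening physical injury | SAE | Other AE |
| Minor self-harm or injury | Other AE | Other AE |
| Admission after self-harm or injury | Depends on threat to life | Not on the SAE list |

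The second and third rows are where the two rules clearly disagree.

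**2. Route for a life-threatening self-harm or injury event**

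- Classified by the criterion: SAE, reported on becoming known.
- Classified by the list and judged likely related: reported outside the quarterly cycle.
- Classified by the list and judged unrelated: quarterly collation only.

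This takes the relatedness condition in the reporting sentence to apply to AEs and not to SAEs. Only the third branch is a gap.

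**3. Quarterly interval against the 8-week intervention**

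Inputs: 8 weeks = 56 days (Intervention and control); intended start 3 January 2025 and first baseline data 12 November 2024 (Procedure). A quarter is taken as Q = 90 to 92 days, or 91 days for 13 weeks.

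- End of 8 weeks for a pupil starting on the intended date: 3 January 2025 + 56 days = 28 February 2025.
- Quarter counted from the intervention start: 3 January 2025 + 91 days = 4 April 2025, which is 35 days after the 8 weeks end.
- Calendar quarter: 31 March 2025, which is 31 days after.
- Quarter counted from the first baseline data: 12 November 2024 + 91 days = 11 February 2025, which falls inside the 8 weeks.

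The answer therefore depends on the start of the quarterly clock. To show the range without choosing a clock, assume that the report date falls at random relative to the pupil's start and that an event is equally likely on any of the 56 days. For an event on day t, the chance that the next report falls by day 56 is (56 − t)/Q. Averaged over t, this is 28/Q. Hence

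P(next report after that pupil's 8 weeks) = 1 − 28/Q

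- Q = 90: 1 − 28/90 = 0.689
- Q = 91: 1 − 28/91 = 0.692
- Q = 92: 1 − 28/92 = 0.696

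Under the same assumption, the chance that some report date falls within a given pupil's 56 days is 56/91 = 0.615. A late report is likely for an event that enters the quarterly route, but not certain.

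**The case against.** The strongest reply is that this is an ambiguity and not a strict contradiction. The word other can be taken to mean AEs that do not meet the threat-to-life criterion. Life-threatening self-harm would then be an SAE, and only lesser self-harm would be an other AE. That reading is available. It does, however, require staff to override an explicit placement of self-harm and injury, and a safety definition should not depend on which reading is chosen. The hospitalisation phrase may simply be garbled, which is a reason to clarify it.

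Several points on the other side stand and limit the concern:

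- AEs judged likely related to the intervention do not wait for the quarter.
- Safeguarding procedures apply in parallel, so the delay concerns oversight by the sponsor and committees, not the immediate response to the pupil.
- The stop-go criterion on negative consequences (Table 1) uses any reported negative or adverse effect, whatever its label, so the classification does not by itself alter the progression decision.
- The article condenses a fuller protocol. That protocol and the DMC charter are not shown and may give severity grading and reporting deadlines.

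A reader might infer that the first quarterly listing must arrive after the intervention is over and could protect nobody in the pilot. The article does not support this. It gives no start for the quarters, the January date is only an aim, pupils start when a Link Worker arranges a meeting, and the related-event route bypasses the quarter. Nor does anything in the article make quarterly collation of unrelated, non-serious AEs an error, so fixed listings during delivery would be a preference.

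**Conclusion.** The point holds in a narrow form. The stated seriousness criterion and the two event lists do not agree. Read literally, a life-threatening self-harm or injury event that is judged unrelated is non-serious and reaches the sponsor, DMC and Steering Committee only in the quarterly collation. For an event during the 8 weeks, that collation falls after the pupil's intervention in roughly 69% of cases if the quarterly clock is at random phase. With a fixed clock, it comes 31 to 35 days after the 8 weeks end, or inside them, depending on the start date assumed. These figures illustrate an unstated clock; they are not properties of the plan. The conclusion about classification does not depend on them.

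A separate wording slip does not bear on AE reporting. Data analysis says: "There will be no interim analysis given the short timescale (6 months) that participants are involved in the intervention". The intervention lasts 8 weeks, and 6 months is the follow-up. This is at most a minor correction.

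**What to change.** Under Monitoring adverse events, reconcile the threat-to-life criterion, the SAE list and the list of other AEs. Every event, including self-harm and physical injury, should be classified by the article's own stated seriousness criterion and follow the SAE reporting route when it meets it. Clarify what the hospitalisation item is meant to cover, and make plain that the relatedness condition in the reporting sentence applies to AEs only, if that is what is intended. If the full protocol already settles these points, the article needs only to be brought into line with it. While the text is open, the 6-month phrase in Data analysis can be corrected to refer to follow-up.

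The cost is amendment wording and a few more events reported promptly. No change to the design, the analysis or the quarterly cycle is needed.

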## Discussion

Currently, there are several major gaps in research and implementation of interventions to increase social and community networks for YP. Interventions typically focus on YP perceived to be at risk of loneliness, rather than YP who report low community connection or loneliness. Studies also only report short-term outcomes and do not account for socio-demographic and other risk factors. Whilst specifically for SP, there are no studies which have tested impact using robust methodologies, such as Randomised Controlled Trials with YP. INACT will address these gaps by providing new information on how SP, which has been found to be beneficial in adult settings, can be implemented in schools to benefit YP reporting low community connection or loneliness. INACT will focus on major cities, which have higher rates of loneliness compared to towns and villages [10]. Moreover, the cities selected for INACT have high levels of deprivation where many YP are socially disadvantaged (e.g., experiencing poverty), which are further risk factors for loneliness [10]. This pilot study will help to identify any major barriers to implementation and address them before proceeding to full trial, road test the SP pathway, provide examples of implementation to share with LWs when implementing at scale, and confirm the suitability and robustness of outcome measures with YP.

The NHS Long term plan includes new approaches to supporting YP and bringing together partners in health, social care, education and the voluntary sector. INACT will create bridges between schools, LWs employed in health and social care settings, and voluntary organisations, to overcome the gaps in evidence in understanding what works in reducing loneliness in YP. Additionally, NHS England aims to triple the number of LWs to 9,000 over the next 10 years [53]. Findings from INACT will provide crucial guidance on how, and where, these LWs should be distributed to help tackle the pressing public health need of youth loneliness. If effective, INACT has the potential to lead to reductions in loneliness among YP and mitigate against both mental and physical ill health later in life, improve educational attainment and save health and social care resources. Findings will be communicated via the UCL Social Biobehavioural group website (https://sbbresearch.org/) as well as via conferences, academic papers and via schools and service user groups.
